**Fig. 1 Fig1:**
[figure not shown]
Flow of the patients through the study

### Study outcomes

The *primary efficacy outcome* of the study will be an objectively documented symptomatic recurrence or extension of SVT, symptomatic DVT (proximal or distal), asymptomatic proximal DVT, symptomatic pulmonary embolism (fatal / nonfatal), or death, whichever comes first, during the treatment period.

The *secondary efficacy outcome* will be: the occurrence of asymptomatic recurrence, extension, or asymptomatic distal DVT; the rVCSS score and the VEINES / Sym-QoL questionnaire; the impact of elastic compression therapy on SVT treatment; the association between CRP levels and primary efficacy outcomes; the natural history of SVT in patients allocated to placebo; the evaluation of the prolonged protective effect of mesoglycan after the first 12 months of treatment.

The *safety outcome* will be the incidence of major bleeding, as defined by the International Society on Thrombosis and Hemostasis (ISTH) criteria: fatal and/or symptomatic bleeding in a critical area or organ (e.g., intracranial, intraspinal, intraocular, retroperitoneal, intraarticular, pericardial, intramuscular with the associated compartmental syndrome); and/or in the case of clinically overt bleeding associated with a hemoglobin decrease of at least 20 g/L or requiring transfusion of 2 or more units of packed red blood cells [40].

### Outcome assessment

Patients will receive detailed instructions on how to contact their referral center if symptoms suggestive of efficacy or safety events occur during the course of the study (treatment period and clinical follow-up).

Patients with suspected recurrent SVT or DVT will undergo CCDU. As previously described, whole-leg CCDU will be performed according to a standardized protocol [41]. Briefly, the proximal venous system of the lower limbs (common, superficial, and deep femoral veins, and popliteal vein to the trifurcation) is examined first with the patient lying supine; then the distal venous network (tibio-peroneal and muscular veins) is scanned, with the patient sitting. We do not routinely investigate the anterior tibial veins. Therefore, vein incompressibility is the only diagnostic criterion used to rule in proximal and/or distal DVT and SVT. Patients with symptoms suggestive of PE are investigated with Computed Tomography Pulmonary Angiography (CTPA) or Pulmonary Ventilation (V)and Perfusion (Q) scan. PE is adjudicated in the presence of an intraluminal filling defect involving the principal, lobar, or segmental branches of the pulmonary artery. If the patient dies, the cause of death is adjudicated as "likely" or "unlikely" due to PE based on autopsy findings, if available, or on clinical grounds.

### Data Collection

Data will be recorded on an “Electronic Data Capture” (EDC) system, based on the “Research Electronic Data Capture” online platform (REDCap, produced and distributed by Vanderbilt University and “REDCap Consortium”), in compliance with article n. 13 of the GDPR (EU 2016/769) [42].

The personal data of the subjects enrolled will be treated with maximum confidentiality, according to the terms of Italian law (DL 211/2003 and subsequent amendments and additions) and GDPR [Regulation (EU) 2016/679 of the European Parliament and of the Council of 27 April 2016].

In particular, the subject's personal data will be known only to the principal investigator and his collaborators who follow the patient and collect the treatment consent. Each enrolled subject will be distinguished only by a unique numeric identifier. The use and maintenance of the REDCap platform are guaranteed by an administrator who manages the user's privileges with a flexible and granular authorization system. REDCap applies the permissions granted to each user who connects via a web browser and the SSL encryption protocol. REDCap allows a complete "audit" of the procedures performed by each user by logging all operations on the data, including viewing and exporting. The operational control log stores the date, time, and operating behavior of the user, allowing a complete review and remote monitoring of the clinical study if necessary. All users accessing the EDC platform (the investigators, the members of their staff, and the staff of the Promoter) must complete a training event to increase the reliability, quality, and integrity of the data recorded in the EDC platform. REDCap implementations allow compliance with the most common industry standards and EMA requirements (GCP, Privacy-IT: DL 211/2003 and subsequent amendments and additions, GDPR, and FDA (21-CFR2-Part 11).

### Statistical analysis and sample size

From the available data in the literature we hypothesize a risk of the occurrence of the primary efficacy outcome in the placebo group at the end of the treatment of 15% (that is, a cumulative proportion of 85% of subjects without events) and a 50% decrease in risk in the mesoglycan group (HR = 0.5) [3, 5, 9].

A two-sided log-rank test with an overall sample size of 650 subjects (of which 325 are in the placebo reference group and 325 in the mesoglycan treatment group) achieves a power of 90%, at a significance level (alpha) of 0.025, to identify a difference of 7.2%, between 15.0 and 7.8% (the proportions of subjects with primary endpoint in the placebo and mesoglycan group, respectively) after 12 months of treatment. This corresponds to a hazard ratio (HR) = 0.50. Subjects will be enrolled in the study for 24 months, and 50% of enrollments will be completed in month 12. The calculation considers the loss of subjects enrolled during follow-up of 10.0% in the placebo group and 10.0% in the mesoglycan group. 650 subjects will be enrolled and randomized 1:1 in the two placebo and mesoglycan arms.

This number seems large enough to guarantee the study an adequate “power” (> 0.80) even if the risk of observing the primary endpoint in the placebo group (hazard rate control) is the difference in efficacy between the two treatments (hazard ratio) that will deviate significantly from those hypothesized.

However, an “interim-analysis” is prepared when 3/4 of the subjects (n = 488) are enrolled so that the “Data and Safety Monitoring Committee” can reformulate the number of subjects to be enrolled (“resampling”) to reach the preset study power (90%) if the number of primary endpoint events observed up to then deviates significantly from the expected for the two groups, i.e., if the HR differs from the estimated one (50%) exceeded 5% in absolute value (a lower deviation seems tolerable based on the above simulation).

The alpha error is, therefore, conservatively set at 0.025 (O'Brien-Fleming method).

For the interim analysis, a tabular description of the frequency of the primary efficacy endpoint will be provided to the Committee, stratified by treatment group but without its label (i.e., without identifying the nature of the treatment assigned to each group).

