## Abstract

No data is available about pharmacological secondary prevention of superficial vein thrombosis (SVT) despite 10–15% of patients develop venous thromboembolic complications at 3–6 months after an adequate treatment of the acute phase. To verify efficacy and safety of mesoglycan in secondary prevention of SVT recurrence and venous thromboembolic complications. Phase III multicenter, double-blind, randomized, superiority trial comparing mesoglycan 50 mg bid vs placebo in consecutive patients with a SVT extended at least 5 cm, after the initial 45-day treatment course with fondaparinux 2.5 mg once-daily. Primary efficacy outcome: SVT recurrence/extension, symptomatic venous thromboembolism (VTE), asymptomatic proximal deep-vein thrombosis, death. Primary safety outcome: major bleeding. We hypothesized a 12-month 15% incidence of the primary efficacy outcome in placebo group and a 50% risk reduction in mesoglycan group. A bilateral log-rank test with a sample of 650 patients (randomization 1:1) reach a 90% power, with an α-error of 0.025, of detecting a 7.0% difference (HR = 0.51) after 12 months of treatment, considering a 10% patients drop-out. At deadline (December 31, 2022) 570 patients have been randomized (10% drop rate). Mean age was 63.9 years, 58.8% were women. SVT involved great saphenous vein in 69.3%, small saphenous vein in 13.1%, and collaterals in 17.6% of patients. SVT was the first event in 61.7%, a recurrence in 38.3%, provoked in 50.2% and unprovoked in 49.8%. Patients not experiencing a primary outcome, or not retiring their consent will be followed up to December 31, 2024 when the final data analysis will be performed

ClinicalTrials.gov: NCT03428711.

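### The stated 90% power does not follow from the plan's own inputs: a 12-month primary window gives about 72–77% with 650 patients and about 66–69% with the 570 randomised

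*Protocol article*

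**What the plan says.** Under Statistical analysis and sample size, the Protocol article specifies "A two-sided log-rank test with an overall sample size of 650 subjects", 325 per arm, which "achieves a power of 90%, at a significance level (alpha) of 0.025, to identify a difference of 7.2%, between 15.0 and 7.8"%. The time point is fixed by "after 12 months of treatment. This corresponds to a hazard ratio (HR) = 0.50", and the control risk is the one expected "in the placebo group at the end of the treatment of 15"%. The same section allows for 10% loss in each arm. It also gives accrual over 24 months, with half the patients enrolled by month 12. It then adds "This number seems large enough to guarantee the study an adequate" power, meaning above 0.80, even if the control risk or the hazard ratio departs from what was assumed.

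The Abstract gives the same sample size, alpha and power but a different target: "of detecting a 7.0% difference (HR = 0.51) after 12 months of treatment". It also reports that "At deadline (December 31, 2022) 570 patients have been randomized".

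The Study outcomes section counts the first primary event, "whichever comes first, during the treatment period". The Treatment section sets that period at 12 months. Under Patient flow, the next 12 months are follow-up without study drug, and Study outcomes lists the effect after the first 12 months as a secondary outcome.

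**The concern.** The power of a log-rank test depends on the number of events. With risks of 15.0% and 7.8% over a fixed 12 months, 650 patients cannot produce many more than 74 primary events. That looks too few for 90% power at a two-sided alpha of 0.025. The accrual pattern is a warning sign: when every patient has the same 12-month window, the speed of enrolment has no effect on the event count. It matters only if patients are followed to a common closing date and events after month 12 are counted.

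What is at stake is how a null result is read. Readers would take a non-significant finding from a 90%-power trial as fairly strong evidence against mesoglycan. If the true type II error at the achieved size is about one in three, that reading is wrong.

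**Working it through.** **Inputs.** Two-sided log-rank test, alpha 0.025, 1:1 allocation, 325 per arm, 12-month risks of 15.0% and 7.8%, HR 0.50, 10% loss per arm (Statistical analysis and sample size); primary events in the treatment period only (Study outcomes); 12 months of treatment (Treatment); 570 randomised (Abstract). Assumptions added here: constant hazards, and loss spread exponentially so that 10% are lost over 12 months.

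**Effect size.** ln(0.922)/ln(0.85) = 0.4997, so the body's 15.0% against 7.8% does match HR 0.50. The Abstract's 7.0 points (15.0% against 8.0%) gives ln(0.92)/ln(0.85) = 0.513, in line with its 0.51. Each pair is coherent, but they are two different targets.

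**Events needed for 90% power (Schoenfeld).** D = 4(z₁₋α/₂ + z₁₋β)²/(ln HR)² = 4(2.2414 + 1.2816)²/(ln 0.5)² = 103.3. The Freedman formula gives 112.

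**Events available in 12 months.**
- 650 patients, no loss: 325 × (0.15 + 0.078) = 74.1.
- 650 patients, 10% loss: the control hazard is −ln(0.85) = 0.1625 per year, the mesoglycan hazard is half of that, and the loss hazard is −ln(0.90) = 0.1054. Events per arm are 325 × h/(h + 0.1054) × [1 − exp(−(h + 0.1054))], which gives 46.3 + 24.1 = 70.4.
- 570 patients: 65.0 without loss, 61.8 with loss.

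**Power.** Φ(√D/2 × ln 2 − 2.2414). For D = 70.4 this is Φ(2.908 − 2.241) = 0.748. For D = 74.1 it is Φ(2.983 − 2.241) = 0.771.

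| Case (HR 0.50) | Events | Schoenfeld, α 0.025 | Simulated log-rank, α 0.025 | Schoenfeld, α 0.05 |
|---|---|---|---|---|
| 650, no loss | 74.1 | 77.1% | 74–75% | 84.7% |
| 650, 10% loss | 70.4 | 74.8% | 72% | 82.9% |
| 570, no loss | 65.0 | 71.0% | – | 79.8% |
| 570, 10% loss | 61.8 | 68.5% | 66% | 77.7% |

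At two-sided 0.05 the simulated power with 10% loss is about 80–81% for 650 and 76% for 570. For 650 at alpha 0.025, Freedman gives 71.1% with loss and 73.5% without. With the Abstract's HR of 0.51, 650 patients and 10% loss, Schoenfeld gives 72.3%.

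**The assurance of power above 0.80 (650 patients, 10% loss, Schoenfeld).**

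| Departure | α 0.025 | α 0.05 |
|---|---|---|
| None | 74.8% | 82.9% |
| Control risk 12% | 64% | 74% |
| HR 0.55 | 62% | 72% |
| HR 0.60 | 49% | 60% |

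At alpha 0.025 the base case is already below 0.80. At alpha 0.05 the base case passes, but each of these departures falls below it.

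**What would give about 90%.**
- A two-sided alpha of 0.10, with 70.4 events, gives 89.7%. The text says two-sided 0.025.
- Uniform 24-month accrual with a common close about 7 months after the last patient gives 102 events and 89.7%. A close at 12 months gives 124 events and 94.7%.
- Keeping the 12-month window and alpha 0.025, 90% needs about 954 patients (Schoenfeld) or 1,032 (Freedman) with 10% loss.

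**The case against.** The strongest defence is that the calculation used a longer window than 12 months. The accrual inputs suggest it. The Abstract has event-free patients followed to the end of 2024, when the final analysis takes place. Statistical considerations asks for outcomes to be traced at both 12 and 24 months. The final primary analysis describes event-free proportions over follow-up and states no cut at 12 months. If events were counted to 24 months per patient, with a constant HR and 10% annual loss, 650 patients would give about 126 events and 95% power, or 88% at HR 0.55. For 570 patients the figures would be about 110 events and 92%, or 83% at HR 0.55. On that reading the 90% would be met and a five-point departure in HR would be tolerable.

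This may well explain where the figure came from, but the calculation is not shown, so that remains an inference. It does not make the figure correct. The outcome definition limits primary events to the treatment period, the later effect is a named secondary outcome, and the sample-size text gives its rates after 12 months of treatment. None of the passages cited for the longer window redefines the primary outcome. Counting later events would also assume that HR 0.50 persists once the drug has stopped.

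The interim re-estimation at 488 patients is not a remedy either. It acts when the HR departs from 0.50 by more than 5 points, so at exactly 0.50 it is not triggered.

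Three smaller points stand. The 66–69% for 570 patients assumes 10% loss. The main efficacy test is a covariate-adjusted Cox model, so log-rank power only approximates its power. The gap between the Abstract and the body is minor alone, worth about 2.5 points of power.

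**Conclusion.** The concern holds. On the stated inputs and the stated 12-month primary window, the design yields 70–74 events against about 103 needed. Power at 650 is 75–77% (Schoenfeld) or about 72–75% (simulation), not 90%. At 570 it is about 66–69% with 10% loss and 71% (Schoenfeld) without. The type II error is therefore about 23–28% at 650 and 29–34% at 570, against the 10% claimed. The shortfall does not depend on how dropout is treated, nor on which of the article's two significance levels applies, since two-sided 0.05 still gives only about 80–85% at 650. The figures assume constant hazards, HR 0.50 and a control risk of 15%. The assurance of power above 0.80 under departures is wrong at alpha 0.025 and does not survive the departures tested at 0.05.

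**What to change.** In Statistical analysis and sample size and in the Abstract:

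1. State the power for the 12-month primary outcome: about 72–75% for 650 patients and 66–69% for the 570 randomised, at two-sided alpha 0.025 with 10% loss. If the level is settled at two-sided 0.05, the figures are about 81–83% and 76–78%.
2. Give the expected number of primary events: about 70 for 650 patients and 62 for 570.
3. Delete the assurance of power above 0.80.
4. Use one target effect throughout: 15.0% against 7.8%, 7.2 points, HR 0.50.
5. Do not present the calculation as if follow-up to a common closing date added primary events.

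The change is to wording only. It needs no extra patients and leaves the outcome and the analysis as they are. The cost is a less favourable power statement, which should also accompany the interpretation of any non-significant result.

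### The stated 90% power is not delivered: a 12-month primary outcome in 650 patients yields about 70–74 events, HR 0.50 at two-sided 0.025 needs about 103, and power is about 72–77%

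*Protocol article*

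**What the plan says.** The section on statistical analysis and sample size gives a full set of design inputs:

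- **Test and size:** "A two-sided log-rank test with an overall sample size of 650 subjects", split equally at 325 per arm.
- **Placebo risk:** the event risk is set "in the placebo group at the end of the treatment of 15% (that is, a cumulative proportion of 85% of subjects without events").
- **Effect:** 15.0% against 7.8% after 12 months of treatment. "This corresponds to a hazard ratio (HR) = 0.50".
- **Loss and accrual:** 10% loss in each arm; 24 months of enrolment, half of it complete by month 12.
- **Claim:** the design "achieves a power of 90%, at a significance level (alpha) of 0.025, to identify a difference of 7.2%, between 15.0 and 7.8"%.

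The abstract repeats the claim ("A bilateral log-rank test with a sample of 650 patients (randomization 1:1) reach a 90% power") with slightly different effect figures: "detecting a 7.0% difference (HR = 0.51) after 12 months of treatment, considering a 10% patients drop-out".

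Under Study outcomes, the primary outcome is the first of several thrombotic events "or death, whichever comes first, during the treatment period". The Treatment section sets that period at 12 months. Protection after the first 12 months is listed separately, as a secondary outcome.

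The article gives neither a required number of events nor the total study duration used in the calculation.

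**The concern.** The power of a log-rank test depends on the number of events. Fixing the primary outcome to a 12-month window fixes the number of events that 650 patients can supply, whatever the accrual pattern. That number falls well short of what the stated error rates require, so the 90% fails for the planned effect itself, before any assumption turns out wrong.

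Three things depend on the figure:

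- **Type II error.** The risk of missing a halving of the hazard is more than twice the stated 10%.
- **Robustness claim.** The same section says power stays above 0.80 even under marked departures from the assumptions. At alpha 0.025 it is below 0.80 with no departure at all.
- **Interim resizing.** The resizing aims at the preset 90% and is triggered when the observed HR departs from 0.50 by more than 5%. A trial running exactly to plan would trigger nothing and stay at about 72–77%.

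A reader who trusts the 90% would also give a null result too much weight as evidence against a halving of risk.

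**Working it through.** **Inputs** (section on statistical analysis and sample size, unless noted)

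- 325 patients per arm; two-sided alpha 0.025, z = 2.2414; power 90%, z = 1.2816.
- 12-month placebo risk 0.150; HR 0.50.
- Loss of 10% per arm, taken here as exponential over 12 months. This form is an assumption, because the article does not specify it.
- Event window of 12 months per patient (Study outcomes and Treatment sections).

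**1. The effect figures agree with each other.** Under proportional hazards the mesoglycan risk is 1 − 0.85^0.5 = 0.0780, which matches the stated 7.8% and the 7.2-point difference.

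**2. Events needed for 90% power**

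- Schoenfeld: 4 × (2.2414 + 1.2816)² / (ln 0.5)² = 103.3.
- Freedman: (2.2414 + 1.2816)² × (1.5/0.5)² = 111.7, so 112.

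**3. Events expected with 650 patients**

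- No loss: 325 × (0.150 + 0.078) = 74.1.
- With loss: for hazard h and loss rate g per 12 months, the probability of an observed event is h/(h+g) × [1 − exp(−(h+g))]. Here g = −ln 0.90 = 0.1054, and h = −ln 0.85 = 0.1625 for placebo or 0.0813 for mesoglycan. The probabilities are 0.1426 and 0.0741, so events = 325 × 0.2167 = 70.4.

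A window of 12 months per patient makes the accrual inputs irrelevant to these counts.

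**4. Power** = Φ(0.6931 × √D / 2 − z), where D is the number of events

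| | D = 74.1 (no loss) | D = 70.4 (10% loss) |
|---|---|---|
| Two-sided 0.025, formula | Φ(2.983 − 2.241) = 77.1% | Φ(2.909 − 2.241) = 74.8% |
| Two-sided 0.025, simulated log-rank (20,000 trials per setting) | 75.0% | 71.9% |
| Two-sided 0.05, formula | 84.7% | 82.9% |
| Two-sided 0.05, simulated log-rank | 83.3% | 80.7% |

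A separate simulation of 4,000 trials per setting gave 74.5% and 71.7% at 0.025. Freedman's formula gives 73.5% and 71.1%. A two-proportion test without loss gives 74% and would need 482 per arm. The methods differ by a few points, and none comes near 90%.

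**5. Where 90% could come from**

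- *Events after month 12.* Reaching 103 events takes about 17 months of event time per patient without loss and nearly 19 with it. With uniform 24-month accrual and follow-up to a common end date, a 30-month total gives 98–106 events (88–91% power) and a 36-month total gives 124–138 (95–97%).
- *One-sided alpha 0.05.* With 70–74 events the formula gives 90–91%.

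**6. Effect for which 650 patients do give 90%.** With no loss and HR 0.43, the mesoglycan risk is 6.7%, D = 70.7 and power is 90.4%. With 10% loss and HR 0.42, the risk is 6.6%, D = 66.7 and power is 90.3%.

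**7. The 570 patients reported as randomised.** At HR 0.50, D = 65.0 without loss and 61.8 with it, giving 71.0% and 68.5% power at two-sided 0.025.

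**The case against.** The strongest reply is that the documents do not establish what was calculated. Accrual of 24 months with half enrolled at month 12 is the kind of input a staggered-entry program asks for, and it matters only if follow-up varies with entry date. The article omits the total duration, which a full protocol may give. A total of about 30 months reproduces the 90%. Some text could suggest longer counting: the abstract places the final analysis after follow-up to December 31, 2024, and the statistical considerations mention efforts to obtain outcomes at both 12 and 24 months. On this view the fault is a mismatch between calculation and endpoint, and quoting one true power is too firm.

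Part of this stands. The source of the 90% is unknown, and a longer event window is a plausible one. It does not rescue the figure. The outcome definition is confined to the treatment period, the power statement itself refers to 12 months of treatment, and later protection is a secondary outcome. Patients also receive no experimental treatment after month 12, so the on-treatment HR could not simply be carried forward. The one-sided reading contradicts the stated two-sided 0.025.

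Two further objections have some force. Interim resizing shows that 650 was not treated as final, but it does not make the base figure correct. And 650 is no longer the operative number: the abstract reports 570 randomised, which lowers power further.

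**Conclusion.** The concern holds. For the primary outcome as defined, 650 patients supply about 70–74 events against about 103 required (112 by Freedman). Power for 15.0% against 7.8% at two-sided 0.025 is about 72–77%, a shortfall of 13 to 18 percentage points. The 90% is missed at the two-sided 5% level as well (about 81–85%).

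The result assumes constant proportional hazards over the 12 months, and loss between none and 10% spread exponentially over that period. Removing 10% of patients outright would be harsher: 66.7 events and 72.2% power by formula. The calculation does not depend on accrual. The conclusion would change only if events after month 12 counted towards the primary outcome or the test were one-sided at 0.05, and the article's present text says neither.

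**What to change.** In the sample-size section and the abstract:

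1. Replace the 90% statement. With 650 patients and a 12-month primary window, about 70 events are expected after 10% loss. That gives about 72–75% power at two-sided 0.025, and about 81–83% at two-sided 0.05, for 15.0% against 7.8%.
2. Add that 90% power at 650 patients and two-sided 0.025 applies only to HR about 0.42 or lower.
3. State the event count and the 12-month window per patient behind the figure. If the calculation used a longer window or a one-sided test, say so and reconcile it with the outcome definition and the stated two-sided alpha.
4. Give the power for the 570 patients randomised beside it (about 69–71% by formula at HR 0.50), so that the figure describes the trial being analysed. Use one set of effect figures in the abstract and the main text.

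The cost is wording and a less favourable power figure. No extra patients are asked for, and the endpoint, test and conduct of the trial stay as they are.

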## Materials and methods

### Design of the study

The METRO study is a multicenter, phase 2, randomized, double-blind, superiority trial that compares mesoglycan 50 mg BID with a matching placebo. Using a placebo as a comparator is justified by the absence of scientific evidence on the efficacy and safety of any treatment in this setting. The METRO study is conducted in 19 Italian Units of Vascular Medicine, all with significant experience in the management of VTE. The Coordinating Centre will be the General Medicine Unit and the Thrombotic and Haemorrhagic Disorders Unit at the Department of Medicine—Padua University Hospital, Italy. The study protocol has been reviewed and approved by the Ethics Committee of the Padua University Hospital, Italy, and by those of each participating center.

Before inclusion, patients/participants are requested to sign a written informed consent form.

An independent data safety monitoring board (DSMB), blinded to the patient's treatment allocation, formed by three highly qualified clinicians in the field of VTE, will adjudicate all efficacy events, monitor patients' safety, and vouch for the data quality.

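### The interim resizing trigger (observed HR more than 0.05 from 0.50) is breached about 78% of the time when the design is exactly right, cannot be read from unlabelled arms, and is not covered by the O'Brien-Fleming provision

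*Protocol article*

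**What the plan says.** All of the rule stands in the protocol article under Statistical analysis and sample size. The design assumes a primary-outcome risk "in the placebo group at the end of the treatment of 15"% and is sized "to identify a difference of 7.2%, between 15.0 and 7.8"%; "This corresponds to a hazard ratio (HR) = 0.50". The test is described as "A two-sided log-rank test with an overall sample size of 650 subjects" that "achieves a power of 90%, at a significance level (alpha) of 0.025". Accrual runs for 24 months with half enrolled by month 12, and 10% loss is assumed in each arm.

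An interim analysis is planned at three quarters of enrolment (n = 488). The committee may then reset the number to be enrolled, so as to restore 90% power, "if the HR differs from the estimated one (50%) exceeded 5% in absolute value". Smaller deviations are called tolerable. The committee receives event frequencies "stratified by treatment group but without its label (i.e., without identifying the nature of the treatment assigned to each group"). The 0.025 level is described as a conservative setting made because of this interim and is attributed to O'Brien-Fleming. The article gives no cap or floor on N and no adjusted final statistic.

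The Abstract reports that recruitment ended at a deadline of 31 December 2022 with 570 randomised, and that the final analysis follows the end of follow-up on 31 December 2024. The article does not say whether the interim was held.

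**The concern.** There are three difficulties. A tolerance of 0.05 on the HR can work as a trigger only if the interim HR is estimated to roughly that precision; otherwise chance decides whether the sample size is reopened. The trigger also needs a directional HR (mesoglycan over placebo), while the committee is given arms it cannot name. Finally, letting the observed treatment effect change N alters the null distribution of the ordinary final test. O'Brien-Fleming boundaries deal with repeated testing for efficacy, not with this.

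At stake are the credibility of the final sample size and the meaning of the 0.025 level. A reader of the results will need to know whether the stop at 570 owed anything to by-arm data.

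**Working it through.** **Inputs from the article.** Placebo 12-month risk 15.0%, mesoglycan 7.8%, 10% loss per arm, 1:1 allocation, 24-month accrual, interim at 488 (0.75 × 650 = 487.5), endpoint counted during the 12-month treatment period (Study outcomes). **Assumed:** exponential events and losses, and uniform accrual, so patient 488 enters at about month 18.

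**The plan's own figures.** HR = ln 0.922 / ln 0.85 = 0.4997, so 0.50 is reproduced. The 90% power is not. Schoenfeld's formula needs 4 × (2.241 + 1.282)² / (ln 0.5)² ≈ 104 events. A 12-month window with 10% loss gives about 46.3 + 24.1 = 70, and power of about 75%. That shortfall is a separate matter and does not affect how often the trigger is breached.

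**Expected events at the interim.** Annual hazards are 0.1625 (placebo), 0.0812 (mesoglycan) and 0.1054 (loss). For event hazard λ and total hazard s = λ + 0.1054:
- full 12 months: (λ/s)(1 − e^−s) = 0.1426 placebo, 0.0741 mesoglycan;
- follow-up uniform over 0 to 12 months: (λ/s)[1 − (1 − e^−s)/s] = 0.0745 and 0.0382.

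At month 18 one third of the 488 have full follow-up and two thirds have uniform partial follow-up:
- placebo: 244 × (0.1426 + 2 × 0.0745)/3 = 23.7;
- mesoglycan: 244 × (0.0741 + 2 × 0.0382)/3 = 12.2;
- total: about 36.

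**Precision.** SE(log HR) = √(1/23.7 + 1/12.2) = 0.352. The 95% range under a true 0.50 is 0.50 × exp(±1.96 × 0.352) = 0.25 to 1.00.

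**Chance of breaching the tolerance when HR is truly 0.50.** P = 1 − [Φ(ln 1.1 / SE) − Φ(ln 0.9 / SE)].

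| Interim data | Events | SE | P(outside 0.45–0.55) |
|---|---|---|---|
| At 488th enrolment | 36 | 0.352 | 0.776 |
| All 488 with complete 12 months | 53 | 0.290 | 0.729 |

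Patient-level simulation gives 0.780 and 0.730. If the 5% is read as relative (0.475 to 0.525), the figures are 86% to 89%. About 738 events would be needed for the trigger to fire no more than 20% of the time, which is more than the 650 patients planned.

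**Direction.** Two unlabelled arms give the HR only up to its reciprocal. Totals can help: at 15% placebo risk, HR 0.50 gives about 24 and 12 events (36), while HR 2.0 gives about 24 and 45 (68). But if the placebo risk were 7.8% and the mesoglycan risk 15.0%, the expected unlabelled table would again be 24 and 12, exactly as under the design.

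**Type I error.** Simulated score paths under no effect, with N reset to 90% power at the observed unlabelled HR and an unadjusted final test at 0.025:
- N may only stay or fall: about 0.026;
- events may grow to 1.5 to 3 times plan: about 0.028 to 0.034;
- an extreme 20-fold ceiling: up to about 0.041.

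The ceilings are assumptions because the article states none. For comparison, a two-look O'Brien-Fleming design at overall 0.05 leaves a final level of about 0.048 (interim at half the information) or 0.044 (at three quarters), not 0.025.

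**The case against.** **Recruitment is over.** It closed at 570, below 650, so no upward resizing took place. A reader might infer that the rule distorted the trial's size. The article does not show that: a calendar deadline explains 570 equally well, and if it alone set N, resizing caused no inflation. This stands, and it moves the remedy from redesign to disclosure.

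**The 0.025 level is a provision for this interim.** A reader might infer a false-positive rate above 5%. The described rule stays below 0.05 in the scenarios run. It passes 0.05 only if the final test used the general 5% level in Statistical considerations, or under a worst-case choice of N with all 488 complete, cuts almost to the interim size and at least fourfold expansion allowed. This also stands: the excess is over 0.025, not over 0.05.

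**The committee may act but need not.** The wording is permissive, so it does not say that N is automatically reset. But a permission open about three times in four under the planned effect does not discriminate.

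**Unlabelled tables are not wholly uninformative.** Event totals separate HR 0.50 from 2.0 if the placebo risk is as assumed, and balanced follow-up lets counts approximate the HR (12.2/23.7 = 0.515). Both are fair. The first fails when the placebo risk is itself uncertain, which is part of what the interim is meant to check.

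**Adjudication.** The board "will adjudicate all efficacy events" (Design of the study), and a reader might infer that seeing the split table biases adjudication. The board is blinded and the table does not reveal any patient's allocation, so the article does not support that.

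**Conclusion.** The concern holds in three limited parts. First, the ±0.05 tolerance is far inside the sampling error. It is breached about 78% of the time at the 488th enrolment and about 73% with complete data when HR is truly 0.50, so calling smaller deviations tolerable supplies no usable threshold. Second, a directional trigger cannot be applied reliably to unlabelled arms. Third, resizing on the observed effect followed by an ordinary test does not hold 0.025 (about 0.026 to 0.034 for the plausible ceilings), although the overall error stays below 0.05; the O'Brien-Fleming label does not justify the procedure. These figures rest on exponential events and losses, uniform accrual, and assumed ceilings on N. The documents do not show that the interim changed anything.

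**What to change.** Before unblinding, state whether the interim was held, when, what table the committee saw, and whether it influenced N or the decision to stop at 570.
- If N was changed because of by-arm data, use a Cui-Hung-Wang weighted final statistic at 0.025, with weights fixed from the event numbers planned before the interim.
- If the calendar deadline alone set N, say so and keep the ordinary test.

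In either case, withdraw the HR ± 0.05 rule and the O'Brien-Fleming justification. Had the interim still lain ahead, the suitable rule would have been blinded re-estimation on the pooled event rate, with HR fixed at 0.50 and a pre-set cap: compare the pooled 12-month risk with the planned (15.0 + 7.8)/2 = 11.4%.

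The cost is a short disclosure and some analysis-plan wording. The weighted statistic loses a little efficiency. Pooled re-estimation would not have rescued an over-optimistic HR.
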